### Wheat cultivation and product development

#### Wheat cultivation

The cultivation of wheat to be used for this study was carried out at Saleh Pat by Shoaib Corporation and appropriate land was selected. Two cultivars, namely ‘*Faisalabad-2008’ (*agronomically biofortified*)* and ‘*TD-1’* (conventional) were selected by consultation with local experts. After harvesting, the wheat was homogenized for both the variants and stored in the warehouse under standard conditions. Agronomic biofortified was produced by zinc foliar application and was sprayed two times with ZnSO4⋅7H2O at 15 days interval at the heading stage. The conventional low wheat variety was grown in the same conditions, but without spraying.

#### Product development

The post-harvest fortified wheat flour was prepared by adding 80 ppm of zinc to 1kg of conventional ‘low zinc’ variety. The fortification was performed in small batches every 15 days. Fortification was carried out in two steps, first by making a concentrated premix. Initially 3.2 g of Zinc oxide was mixed with 1kg of flour and subsequently added this premix to 19kg conventional wheat in a rotation mixer and mixed and then further 20kg of wheat flour was added to make 40kg bag.

Product development and sensory testing were conducted at the Bahauddin Zakariya University in Multan and the Mithi field site. Each product was developed at different extraction rates and variable fermentation times, considering local contextual factors. The whole wheat product of both varieties and two-hours fermented flatbread were deemed acceptable by the panelists during sensory testing and hence were chosen for the trial. The details would be published in a separate paper.

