Zinc bioavailability from a mixed or vegetarian diet based on refined cereal grains is estimated to be 26–34%, whereas 18–26% is absorbed from an unrefined cereal-based diet [18]. The actual amount of absorbed zinc not only depends on the zinc content of the consumed diet but is highly affected by its intestinal zinc bio-accessibility and bio-availability [18]. The inhibitory effect of phytate on zinc absorption is concentration-dependent and has shown to be more important than the phytate content of the product itself [19]. Fermentation theoretically results in higher zinc bioavailability if a significant reduction of phytate is achieved.

Food fortification with zinc appears as an attractive public health strategy, with numerous programs initiated in developing countries as a cost-effective way to combat zinc deficiency [1, 12]. Systematic reviews evaluating zinc fortification indicate significant improvements in plasma zinc concentration, reduced prevalence of zinc deficiency, increased child weight, and enhanced short-term auditory memory. However, data for adolescents, pregnant women, and lactating women are limited [20]. Biofortified zinc flour have also shown mixed effects [21].

The aim of this randomized controlled trial (RCT) is to assess the effect of fermented and unfermented wheat flour flatbread from agronomically zinc biofortified and post-harvest fortified wheat flour when compared to conventional low-zinc wheat flour flatbread and its impact on health including zinc status, anthropometric outcomes, risk of T2DM and morbidity on adolescent and adult females. In Pakistan, common naan is a type of flatbread, is typically made from fermented maida (all-purpose low extraction) wheat flour, characterized by refined flour with minimal bran and germ. However, in most households, the community usually uses unfermented whole wheat flour flatbread. Wheat samples from various sites across Pakistan were tested, with zinc levels ranging from 20-50mg/kg. The trial chose two wheat varieties: conventional low zinc (20-25mg/kg) and high zinc content which is agronomically biofortified (>35mg/kg) which was grown under collaborator supervision at the study site.

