**Fig 2 pone.0304462.g002:**
[figure not shown]
Study groups.

Group 1: will receive fermented high zinc agronomically biofortified wheat (>35mg/kg) flour flatbread.Group 2: will receive unfermented high zinc agronomically biofortified wheat (>35mg/kg) flour flatbread.Group 3: will receive fortified (post-harvest) whole wheat (80mg/kg) flour flatbread.Group 4: will receive low zinc conventional whole (20–25 mg/kg) wheat flour flatbread.

The intervention duration will be six months, and participants will be provided with the respective ‘flatbread’ with a vegetable curry or pulse (*daal*) meal once a day for six days a week for six months This meal would be distributed at schools/colleges or community spaces during break or after the school is over.

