#### Randomization and allocation concealment

Individuals will be randomly assigned in the four groups (red, blue, green, and black) through a computer-generated random number list. A statistician will assign the individuals into four groups by a computer-generated list and would then assign color codes (red, blue, green, black) without knowing which color belongs to which group. This randomization will be stratified on gender and age (10–13 years, 14-19years, 20–40 years old) and adjusted for serum zinc, BMI, zinc deficiency and HbA1C.

An independent consultant from an international University (University of Sydney) would be responsible for assigning the three intervention and control groups to each color group and will not be involved in the trial, including recruitment, implementation, or evaluation. The consultant would be responsible for generating and safeguarding the code and would be the only person communicating with the flour mill (Shoaib Corporation) and nutrition laboratory to ensure that the correct flour is being milled and packed in the right color bag for each batch. The consultant will break the code when the final data is collected and analyzed.

This flour mill site (Saleh Pat) is located about 500km from the trial site and the flour would be transported fortnightly to the field site. Shoaib Corporation has set up a separate local mill (chakki) for the study and has the warehouse where the two different varieties of wheat are being stored. They would be responsible to mill, fortify (ZnO - 80mg/kg) and pack high zinc, fortified, and low zinc wheat/flour in 40kgs polypropylene sacks, corresponding to a specific color. To ensure accuracy, fortnightly samples of color-coded products will be sent to the laboratory and the results will be shared with the consultant for confirmation.

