## Discussion

Micronutrient deficiency is a serious health concern, which could cause serious health conditions. Malnutrition is a global issue as nearly a quarter of the world’s population is suffering from one or more micronutrient malnutrition disorders. Globally, 22.2% children are stunted, 50.5 million are wasted, and 38.3 million under five children are overweight due to multifaceted malnutrition [46]. The issue of malnutrition is persistently high with slow progress in many developing regions of the world. Zinc deficiency is amongst the common micronutrient deficiency and a major global health challenge, as approximately 17% of the global population does not get enough zinc in their diet. Pakistan has one of the highest rates of zinc deficiency worldwide, affecting 20–40% of the population, with large provincial and regional disparities.

Amongst the many strategies to alleviate zinc deficiency, food fortification is considered a safe and cost-effective measure to prevent zinc deficiency amongst other micronutrient deficiencies. Biofortification of food crops (enhancing micronutrient content using plant breeding techniques) is also a common fortification intervention to increase provitamin A, zinc, iron, and folate contents in staple foods. Agronomic biofortification also increases the crops’ micronutrient mobilization and utilization potential. It is reported to be produced and consumed by over 20 million people globally [47]. The EZZAFAW trial is an evaluation of the efficacy of zinc fortification and will help inform policy for the most suitable strategy to deliver zinc, as this offers a direct comparison of agronomically biofortified and fortified wheat and explores the additional effects of fermentation.

T2DM poses a major public health challenge, due to its increasing prevalence and complex complications. In populations with reduced growth and thin physiques, like in India, there is an elevated risk of truncal obesity and metabolic issues due to sedentary behavior and high-glycemic diets, exacerbated by low birth weight [48]. Chronic glucose exposure affects erythrocyte membranes during their long lifespan, leading to structural and functional disruptions.

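### The Group 3 flour is said to receive 80 ppm of added zinc, but the recipe adds 80 mg/kg of zinc oxide, which is about 64 mg/kg of zinc

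*Protocol article*

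**What the plan says.** The dose of the post-harvest fortified flour appears in three places in the protocol article.

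- **Product development, opening sentence:** the flour was "prepared by adding 80 ppm of zinc to 1kg of conventional" low-zinc wheat flour. This names zinc as what is added.
- **Product development, recipe:** "Initially 3.2 g of Zinc oxide was mixed with 1kg of flour and subsequently added this premix to 19kg conventional wheat", and "then further 20kg of wheat flour was added to make 40kg bag". This names zinc oxide and gives its mass and the batch size.
- **Randomization and allocation concealment:** the mill's task is described as "They would be responsible to mill, fortify (ZnO - 80mg/kg) and pack high zinc, fortified, and low zinc wheat/flour", in 40 kg sacks. This again names the oxide.
- **Intervention, list of study groups:** Group 3 "will receive fortified (post-harvest) whole wheat (80mg/kg) flour flatbread". This does not say whether the figure is zinc or oxide, added or total.

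The base flour is the conventional wheat. The Introduction gives the zinc content of both wheats: "The trial chose two wheat varieties: conventional low zinc (20-25mg/kg) and high zinc content which is agronomically biofortified (>35mg/kg" as a lower limit for the second. No section converts zinc oxide to elemental zinc.

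**The concern.** A mass of zinc oxide is not the same mass of zinc, because about a fifth of the oxide is oxygen. The same figure, 80 mg/kg, is attached once to zinc and once to the oxide, so one of the two labels must be wrong.

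This is the dose of one of three active interventions. The Discussion says of the trial that "this offers a direct comparison of agronomically biofortified and fortified wheat", and that comparison can only be interpreted if the zinc content of each product is known. The protocol also records the weight of flatbread eaten (Compliance) and plans to assess a dose-response relation (Trial analysis). Converting bread weight to zinc needs a concentration. If the stated 80 ppm of zinc is carried into the report or used in that conversion, added zinc in Group 3 is overstated by about a quarter. Anyone reproducing the product from the stated zinc dose would use more oxide than the recipe does.

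**Working it through.** **Inputs**

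- Zinc oxide per batch: 3.2 g = 3,200 mg (Product development).
- Batch: 1 kg premix + 19 kg + 20 kg = 40 kg (Product development; the Randomization section also gives 40 kg sacks).
- Stated addition: 80 ppm of zinc = 80 mg/kg (Product development).
- Base flour zinc: 20–25 mg/kg (Introduction; list of study groups).
- Zinc fraction of zinc oxide: 65.38 / (65.38 + 16.00) = 65.38 / 81.38 = 0.803. These are atomic weights, not figures from the documents, and the oxide is taken as pure.

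**Reproducing the figure of 80**

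3,200 mg / 40 kg = 80.0 mg/kg of zinc oxide. The recipe reproduces 80 exactly, but for the oxide.

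**Zinc actually added by the recipe**

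80.0 × 0.8034 = 64.3 mg/kg. Shortfall against the stated 80: 80 − 64.3 = 15.7 mg/kg, or 19.7%. In the other direction, 80 / 64.3 = 1.245, so quoting 80 overstates added zinc by about a quarter.

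**Other readings that might rescue 80 ppm of zinc**

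| Reading | Calculation | Result |
|---|---|---|
| 20 kg stage instead of 40 kg | 3,200 × 0.8034 / 20 | 128.5 mg/kg |
| Batch size that would give 80 | 2,571 mg zinc / 80 | 32.1 kg, not 40 kg |
| 80 as total zinc | 64.3 + 20 to 64.3 + 25 | 84.3–89.3 mg/kg |
| Impure oxide, 95–99% (assumed range) | 64.3 × 0.95 to 64.3 × 0.99 | 61.1–63.6 mg/kg |

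None gives 80, and impurity widens the gap.

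**Oxide needed for 80 ppm of zinc**

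80 × 40 / 0.8034 = 3,983 mg, about 3.98 g per 40 kg bag: 0.78 g more than the recipe.

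**Total zinc under each statement**

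By the recipe: 84.3–89.3 mg/kg. With 80 ppm of zinc added: 100–105 mg/kg. The ranges do not overlap; the smallest gap is 100 − 89.3 = 10.7 mg/kg.

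**Size on the trial's own scale**

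- At the stated limits, biofortified flour exceeds conventional flour by at least 35 − 25 = 10 to 35 − 20 = 15 mg/kg. The 15.7 mg/kg discrepancy is as large as that minimum contrast.
- Table 1 (unfermented) gives 1000 / (1000 + 4 + 30 + 300) = 0.75 g of flour per g of dough. Two balls of 120–125 g (the text and the table give these two weights) hold about 180–187 g of flour. Added zinc per meal is then about 11.6–12.0 mg by the recipe and 14.4–15.0 mg by the stated dose, a difference of nearly 3 mg.

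**The case against.** The strongest defence is that this is loose wording and not a dosing error. The operational instruction is complete: compound, mass, mixing steps and bag size are all given, the arithmetic closes exactly, and the milling description names the oxide at the same level. Only one noun in a summary sentence is off, and a reader who follows the explicit 3.2 g makes the intended product. No analysis is stated to use the figure of 80.

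The Group 3 label in the list of study groups can also be defended. The other figures in that list are zinc contents of wheat, so by parallel 80 mg/kg may mean total zinc. The recipe's 84–89 mg/kg is only about 5–12% above it.

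Finally, the delivered level is checked: "fortnightly samples of color-coded products will be sent to the laboratory and the results will be shared with the consultant for confirmation".

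Much of this stands. The wording is the likelier error, the arm label may be roughly right as a total, and the assays limit the practical risk. None of it makes the statement about added zinc correct: that sentence speaks of adding zinc, and the recipe beneath it does not add that amount. Assay results sent to the consultant do not correct the published text. It is also fair that the documents give no assay precision, so a single sample might not separate the two dose levels even though the nominal ranges do not overlap.

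**Conclusion.** The concern holds. The stated addition of 80 ppm of zinc and the recipe of 3.2 g zinc oxide per 40 kg are incompatible: the recipe adds about 64.3 mg/kg of zinc, 19.7% below the stated figure. Which statement is wrong is not settled by the document, although the exact fit of the recipe to 80 mg/kg of oxide, together with the milling description, points to the word zinc.

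The result rests on the zinc fraction of pure zinc oxide; lower purity makes the shortfall slightly larger. The total-zinc figures also assume base flour within the stated 20–25 mg/kg.

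The consequence is limited to the description and interpretation of the Group 3 dose. The randomised comparison and the sample size are not affected. It should be corrected, because it is the stated dose of a randomised intervention and the correction is nearly free.

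**What to change.** 1. Establish which figure is right from the mill's fortification records and the fortnightly assay results. Several batches taken together are safer than one sample. Route the check through the independent consultant, who already deals with the mill and laboratory, or leave it until the code is broken: zinc results by colour would reveal the fortified arm to the study team.
2. If the recipe is right, restate the Group 3 dose as 80 mg/kg zinc oxide, about 64 mg/kg added zinc, with total zinc of about 84–89 mg/kg. If 80 ppm of elemental zinc was in fact added, correct the oxide mass to about 3.98 g per 40 kg bag.
3. Wherever 80 mg/kg or 80 ppm appears (the list of study groups, Randomization and allocation concealment, Product development), say whether it is zinc or zinc oxide, and added or total.
4. If zinc intake is calculated for the dose-response assessment, use the confirmed elemental zinc content.

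The cost is a wording correction and a look at records and assays the plan already provides for. No new procedure or measurement is needed.

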### Intervention delivery

#### Flatbread preparation, and delivery

The flatbread and the vegetable/pulses curry will be prepared in the study kitchen established at the study site and professional catering staff will be hired to prepare food following standard guidelines. Four color-coded tandoor ovens will be set up, and the designated kitchen staff for each group will wear color-matched uniforms. The regular menu will feature flatbreads with a choice of vegetable curry or pulses, designed weekly and prepared in the study kitchen to ensure consistency.

High zinc fortified flour and low zinc wheat flour will be mixed separately with water, salt, oil in their respective color-coded utensils. The ingredients will be kneaded by hand to form soft dough. The dough will then be covered with a muslin cloth and the resting time of the dough will be kept identical for each of the produced flour portions (30 min) (Table 1) For fermented flour, we will add 3.5g yeast /kg of flour and let the dough rest for 2hrs at 30 degrees Celsius.

**Table 1 pone.0304462.t001:** Ingredients for flatbread.

Ingredients	Unit	Quantity	
		Fermented	Unfermented
Wheat flour	g	1000	1000
Active dry yeast	g	3.50	-
Iodized Salt	g	4	4
Ghee/cooking oil	g	30	30
Water for kneading the dough	ml	300	300
One ball of dough	g (±5g)	125.00	
Weight of one ready cooked flatbread	g (±5g)	100.00	

Each ball will be weighed on a weighing machine to ensure that each ball has a weight of 120 grams. It will be transferred to a baking tray or round cushion lined and these will be used to place the flatbreads inside separate tandoors for each group. To allow for proper rising, flatbreads will be spaced adequately inside the tandoor. Prepared flatbreads will be packed in color coded lunch boxes and each box will have two flatbreads (each flatbread divided in four equal parts) and curry under supervision. These boxes will then be transported to the targeted schools/colleges/community space and packing will ensure that the freshness of flatbread is maintained.

#### Procedure of serving flatbread/curry in schools

Field staff will deliver the respective lunchbox to the specific group in each school. The adolescents in different groups in a single school/college would be segregated and seated in separate marked rooms. The lunch boxes would be delivered after matching participants’ specific IDs on the box with the student badges. The staff will also have extra flatbreads in color-coded bags and would give to individuals who would demand for more. The study team will record the amount of flatbread consumed by each participant for each day and data recorded electronically on an android app. Research staff and teachers will ensure each participant receives their designated lunch, record food consumption, and maintain order, ensuring that food is not being shared or taken home.

### Data collection

Baseline and endline measurements will be conducted for all participants, whereas for midpoint assessments, sampling scheme will be assessed by randomized, arm-based stratified selection so that a third from each arm is tested at two additional time points.

For all study visits, electronic app-based questionnaires will be used to guide personnel in conducting structured interviews with the study participants at baseline and endline. Data on 24-hr dietary recall will be collected in paper-based questionnaires. A summary of all monitoring and visit-specific forms will be used throughout the study.

### Hiring and training

All staff would be hired after a rigorous scrutiny process and a preference would be given to local people as they are most aware of the local customs and language. Upon recruiting, the research staff would undergo a comprehensive eight-day training and refresher training at midline and before endline assessments. The training will cover areas of line listing, mobile app data collection, anthropometric measurements, blood pressure measurements, blood sampling, food handling and ethical conduct and adherence to regulations. Kitchen staff will receive comprehensive training on handling wheat, flour, dough, flatbread preparation, weighing methods, hygiene, and food packing.

### Pilot testing

Survey questionnaires will be pilot tested with a small group of participants (maximum 50) for response latency, question interpretation and appropriateness. Face validity and construct validity for all questionnaires will also be conducted with a small expert group with knowledge in public health and nutrition epidemiology.

### Baseline, midline, and endline data collection

Participants will undergo assessments at baseline and endline, where we will gather data on socio-demographic factors, dietary intake via 24-hour dietary recall, anthropometric measurements (weight, height, MUAC, waist circumference), blood pressure measurements, and blood samples will be collected for biochemical analysis, including serum zinc levels, FBS, HbA1C, and insulin at both time points. Lipid profile and RBC membrane fatty acids will be assessed only at the endline. At midline, we will conduct 24-hour dietary recalls, measure serum zinc and HbA1C for a subset from each group. The data for morbidity (diarrhea and ARI) will be collected fortnightly for the entire duration of the intervention.

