### Outcomes

#### Primary

Serum zinc concentrationZinc deficiencyHbA1CHOMA-IR (cut-off >2) [24]Lipid profile (total cholesterol, very low-density lipoprotein (VLDL), low-density lipoprotein (LDL), high-density lipoprotein (HDL); triglycerides (TGs))

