### Trial analysis

This trial will adhere to CONSORT guidelines for randomized trials, with primary analysis on an intention-to-treat basis [22]. Both primary and secondary data will be analyzed following the same principle. Descriptive statistics will include mean and standard deviation for symmetrically distributed continuous variables, median and interquartile range for asymmetrically distributed ones, and frequency with percentages for categorical data. Associations between dependent and independent categorical variables will be accessed using chi-square test, while one-ANOVA will be used to assess difference in continuous outcomes by intervention groups. Significant association further assessed by post-hoc test adjusting for multiple comparisons. Multivariate analysis will be performed using mixed effect linear or logistic regression to assess the impact of intervention over time by including time and group interaction. The time and intervention group will be treated as fixed effect while students included in the model as random intercept. The potential confounding factors that are imbalance at baseline will also be included as fixed effect in the model. The minimal adequate model for regression will be computed using the backward procedure. Statistical Significance will be set at p-value of <0.05. To assess the robustness of the findings, a sensitivity analysis will be conducted, and a dose-response relation will also be assessed.

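### Lipids and RBC fatty acids are measured once, at endline, so the only covariate-adjusted model in the plan, a time-by-group mixed model, cannot be fitted to them

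*Protocol article*

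**What the plan says.** The Primary outcomes list has five entries. The first four read "Serum zinc concentrationZinc deficiencyHbA1CHOMA-IR (cut-off >2") and the fifth is "Lipid profile (total cholesterol, very low-density lipoprotein (VLDL), low-density lipoprotein (LDL), high-density lipoprotein (HDL); triglycerides (TGs"). RBC membrane fatty acid concentrations are listed under Secondary.

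The section on baseline, midline and endline data collection describes blood sampling "including serum zinc levels, FBS, HbA1C, and insulin at both time points" and then makes an exception: "Lipid profile and RBC membrane fatty acids will be assessed only at the endline". Midline blood work covers serum zinc and HbA1c in a subset, and no lipids.

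Trial analysis names two routes for a continuous outcome:

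- A cross-sectional test: "one-ANOVA will be used to assess difference in continuous outcomes by intervention groups", with post-hoc tests adjusted for multiple comparisons.
- A multivariable model: "mixed effect linear or logistic regression to assess the impact of intervention over time by including time and group interaction", with "students included in the model as random intercept". Covariates enter here: "The potential confounding factors that are imbalance at baseline will also be included as fixed effect in the model".

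Neither route is assigned to particular outcomes, and nothing is said about outcomes measured once. Under Randomization and allocation concealment, allocation is stratified on gender and on age (10–13, 14–19 and 20–40 years).

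**The concern.** The multivariable model needs at least two time points per participant, and lipids and RBC fatty acids have one. For these outcomes the only covariate-adjusted analysis in the plan cannot be run, and the analyst is left with an ANOVA that has no covariates.

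That matters because each arm is to combine 210 adolescents with 40 adult women, and each of the women must carry at least one diabetes risk factor to be eligible. Lipid variation between these age and sex groups would go into the ANOVA error term, although the trial stratified on those factors. If the plan stays silent, the adjusted analysis of a primary outcome will be improvised after the data are in.

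**Working it through.** **Inputs.** Primary list, lipid timing, ANOVA and mixed model: as quoted above. From the sample size section: 250 per arm, 10% dropout, power 0.80, alpha 0.05 (two-sided assumed, since sidedness is not stated), serum zinc mean 79.5 and SD 35.9. The document gives no baseline–endline correlation ρ for lipids, so ρ is an assumption, shown from 0.3 to 0.8.

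**1. The plan's own sample size.** It rests on serum zinc and HbA1c; no lipid variable enters. Reading the 0.12 effect size as a 12% relative difference in zinc:

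- Δ = 0.12 × 79.5 = 9.54
- n = 2 × [(1.960 + 0.842) × 35.9 / 9.54]² → 223 per arm
- 223 / 0.90 → 248, close to the stated 250

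Other readings do not give 250 (a standardized difference of 0.12 needs 1,091 per arm before dropout). Nothing below depends on this. I use only 250 × 0.90 = 225 evaluable per arm.

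**2. How many primary outcomes are affected.** One of the five listed entries. Counted by component, it is 5 lipid variables beside 4 others, so 5 of 9.

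**3. Can the mixed model be fitted?** Its fixed-effect columns are an intercept (1), arm indicators (3), time (1) and time-by-arm terms (3), 8 in all. With a single time point, the time column is a multiple of the intercept and each interaction column is a multiple of its arm column. The rank is 4, so time and interaction effects are not estimable. In the linear model with one value per person, Var(Y) = σ²(participant) + σ²(residual), and only the sum is identified. The random intercept therefore cannot be separated from residual error. What remains is a four-group comparison at endline.

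**4. What a single measurement costs in precision.** The smallest detectable pairwise difference, in SD units, with no multiplicity correction:

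- Endline only: (1.960 + 0.842) × √(2/225) = 0.264
- Adjusted for own baseline: 0.264 × √(1 − ρ²)
- n per arm that an endline-only analysis would need for the same precision: 225 / (1 − ρ²)

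| Assumed ρ | Detectable difference (SD) | Equivalent n per arm |
|---|---|---|
| none (endline only) | 0.264 | 225 |
| 0.3 | 0.252 | 247 |
| 0.5 | 0.229 | 300 |
| 0.6 | 0.211 | 352 |
| 0.7 | 0.189 | 441 |
| 0.8 | 0.158 | 625 |

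**5. What can be recovered without baseline lipids.** The same formula applies with ρ² replaced by the R² that gender, age band and other baseline covariates jointly explain in endline lipids. The document gives no R². For illustration, R² = 0.09 would give 0.252 SD and R² = 0.25 would give 0.229 SD. The covariates are available: weight, height, HbA1c, fasting glucose and insulin are all taken at baseline, which yields BMI and HOMA-IR.

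**The case against.** The strongest reply is that a valid analysis of lipids is already stated. One-way ANOVA on endline values can be run, is unbiased under randomization, and reflects chance imbalance in its standard error. Stratification balances the age and sex mix across arms. A primary outcome does not need a baseline value, and no lipid power target is missed because none was set. An article also commonly leaves the outcome-by-outcome model to the full analysis plan.

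Most of this stands, and it rules out several stronger readings that a reader might infer:

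- *That no baseline adjustment is possible.* Only the participant's own baseline lipid value is missing; other baseline variables can be used.
- *That the plan requires the mixed model for every outcome.* The sentence that puts primary and secondary data under one principle follows the intention-to-treat statement and refers to that.
- *That most primary variables have no analysis.* Lipids are one of five listed entries, and the ANOVA is available for them.
- *That the lipid comparison is biased.* The documents give no ground for this; the loss is one of precision and of any estimate of change.
- *That lipids must be moved to secondary.* This would alter the primary set of a registered trial that has been enrolling since August 2023, and it is not needed to resolve the mismatch.

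One part of the reply does not stand. The article is not merely silent on detail: it names one adjusted model, ties covariates to it, and elsewhere fixes a measurement schedule on which that model cannot run for a primary outcome. Balancing on gender and age band by design is also no reason to leave them out of the model. An analysis that ignores stratification factors related to the outcome leaves their variation in the error term and overstates the standard error.

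**Conclusion.** The concern holds in a limited form. For the lipid profile (one of five primary entries, with five components) and for RBC fatty acids (secondary), the time-by-group mixed model with a random intercept cannot be estimated. As written, these outcomes fall back to an unadjusted endline ANOVA. That comparison is valid but less precise than the data allow, and it cannot show change.

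The non-estimability is certain if lipids are measured once, as stated. The SPIRIT schedule figure is not shown and could not be checked; the general remark under Data collection that baseline and endline measurements are done for all participants does not override the specific lipid statement. The size of the precision loss is not certain: 0.264 SD against 0.252 to 0.158 SD depends wholly on an assumed ρ, and it measures the gap to own-baseline adjustment, which the wording fix can close only in part.

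**What to change.** Add to Trial analysis that the lipid components and RBC membrane fatty acids are compared between arms once, at endline, by a linear model on group. The model adjusts for gender, age band and prespecified baseline BMI, HbA1c and HOMA-IR. It has no time or time-by-group term and no random intercept, and results are reported as endline differences with no claim of change. Reserve the mixed model for outcomes measured at more than one visit.

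Lipids need not change tier. If baseline serum has been stored, assaying lipids on it would allow own-baseline adjustment. That is optional, and the document does not say whether such samples exist.

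The cost is a wording amendment, notified to the ethical review committee as the protocol provides, and slightly more analysis work. It can be done while the color codes are still blinded. The optional assay would add laboratory cost.
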